# Evaluation of a youth-focused suicide prevention HOPE aftercare service: protocol for a non-randomized hybrid effectiveness-implementation type I design

**DOI:** 10.1186/s12913-024-11795-2

**Published:** 2024-11-13

**Keywords:** Suicide prevention, Aftercare, Young people, Effectiveness, Implementation, Program evaluation

## Abstract

**Background:**

Suicide is the fourth leading cause of death among young people aged 15–29 worldwide. Young people often present to emergency departments (EDs) with self-harm and suicide-related behaviors. The period following discharge from the ED is recognized as one of elevated risk for both repeated self-harm and suicide. During this critical time, suicide prevention aftercare services are recommended. Despite their increased popularity, evidence demonstrating the effectiveness of these models is very limited.

**Methods:**

Using a hybrid effectiveness-implementation type I design, this evaluation will assess the effectiveness and implementation of a suicide prevention aftercare (*Hospital Outreach Post-suicidal Engagement; HOPE*) service designed to reduce risk of self-harm and suicide in young people aged 12–25 who are referred to the service following an ED presentation for self-harm or suicide attempt. Two complementing theoretical frameworks will guide this evaluation, specifically the design, data collection, analysis, and interpretation of results. The RE-AIM evaluation framework will be used to assess *Reach*, *Effectiveness* (including cost-effectiveness), *Adoption*, *Implementation* and *Maintenance* of the HOPE aftercare service. The PRISM implementation framework will be used to assess multi-level contextual factors hypothesized to affect the RE-AIM outcomes. Several data sources will be used to assess the changes in primary and secondary outcomes from baseline to post–intervention, and at follow-up, including user and provider self-report surveys, semi-structured interviews, and routinely collected hospital data. An historical control study will also be conducted using data from the Self-Harm Monitoring System for Victoria to examine the impact of the service on rates of self-harm and suicide-related presentations to ED, and compare trends prior to and following commencement of the HOPE aftercare service. In addition, dynamic systems modelling will be used to assess the future scalability of the service.

**Discussion:**

Findings from this evaluation will determine the effectiveness, including cost-effectiveness, of the HOPE aftercare service and describe the implementation context. They will inform the future development and sustainability of this and other similar services across Australia and internationally.

**Trial registration:**

This trial was prospectively registered with the Australian New Zealand Clinical Trials Registry (ANZCTR) on the 19th December 2023 (Registration number ACTRN12623001332617). We do not foresee any amendments to this protocol however, if any unforeseen modifications are required, they will be submitted to ANZCTR.

## Background

### Rates of suicide

Suicide is the fourth leading cause of death among young people aged 15–29 worldwide [1] and the leading cause of death among young Australians [2]. In 2022, deaths by suicide represented 30.9% of all deaths in young Australians aged 15–17 and 32.4% of all deaths in those aged 18–24 years, up from 16.5% to 23.9% respectively in 2001 [2]. For every young person who dies by suicide, many more engage in self-harm, and more still live with suicidal ideation [3]. Both suicide ideation and self-harm (i.e., intentional drug overdose, self-injury and/or self-poisoning irrespective of motivation and degree of suicidal intent) [4] are the greatest predictors of future suicidal behavior [5, 6]. Whilst many young people do not seek help from services for self-harm, those who do often experience sub-optimal treatment responses [7, 8].

### Presentation rates

Many at-risk young people present to emergency departments (EDs) in crisis, following severe self-harm and/or a suicidal attempt [9]. In Australia, the hospital presentation rates are highest among young people aged 15–19 years (389 per 100,000 population) [10]. The rates of intentional self-harm hospitalization are steadily increasing [11]. The highest hospitalization rates are reported for females aged 15–19 and they have increased from 374 hospitalizations per 100,000 in 2008–09 to 637 hospitalizations per 100,000 in 2021–22 [10].

The risk of further suicide attempt/s is greatest immediately following discharge from the ED after a suicide attempt [7, 12] and remains high for up to 12 months following the attempt [12, 13]. Modelling studies with Australian data estimate that delivering better care at this time would reduce the numbers of self-harm hospitalizations and suicide deaths by 5.65% (95% CI, 4.87 − 6.42%) and 5.45% (4.68 − 6.22%), respectively [14]. This would mean ~ 1,616 fewer hospitalizations and ~ 33 fewer suicide deaths in Australia every year [15] .

### Aftercare service models

In response to this, aftercare services that provide support for people following their presentation to the ED with self-harm/suicidal ideation have received significant attention. Aftercare services typically aim to help an individual bridge the gap between hospital-based care during an acute crisis and establish ongoing support in the community [16]. They can be classified in three categories: brief contact interventions, brief interventions, and coordinated assertive aftercare [16]. Brief contact interventions are low-intensity and low-cost interventions such as supportive messages via postcard, text message or letter, that encourage engagement with services. Milner and colleagues’ [17] meta-analysis showed that brief contact interventions reduced frequency of suicide re-attempts and self-harm. Brief interventions are defined by a limited number of short sessions, with a significant proportion of sessions delivered via telephone, and focus on helping to understand the factors that lead to a suicidal crisis and help expand the individual’s coping strategies. The Attempted Suicide Short Intervention Program (ASSIP) [18] is an example of this approach that has been shown to reduce suicide re-attempts.

Coordinated assertive aftercare typically involves the following four components: (1) immediate follow-up post discharge from hospital, (2) ongoing risk assessment and planning, (3) motivational support to engage with treatment and (4) problem solving/solution-focused counselling [19]. Aftercare is offered over a defined period, usually 3–6 months. Currently there are several models of assertive aftercare globally that have demonstrated varying degrees of efficacy (e.g., Norwegian OPAC [Outreach, Problem Solving, Adherence, Continuity]) (e.g., 3), the AID model in Copenhagen [20], and the ACTION–J model in Japan [21].

In Australia, the Hospital Outreach Post-suicide Engagement (HOPE) aftercare for adults is the first such model implemented in the public healthcare system [22]. To date, there have been few evaluations of this model; an initial evaluation showed substantial improvements to suicidal ideation, distress, coping and wellbeing, among adults [23].

## Orygen’s child and youth-focused HOPE aftercare

Youth-focused HOPE aftercare has been developed based on the adult HOPE model [22]. Currently, there are four youth-specific services delivering HOPE aftercare in Victoria, Australia. The Orygen HOPE aftercare was co-designed in collaboration with young people and families with lived experience and is delivered by Orygen—a state-funded national center for youth mental health responsible for the provision of primary and secondary clinical services. Orygen provides clinical mental health services to young people aged 12–25 in the north–west metropolitan region of Melbourne—a large and diverse geographical area with high population growth. Of the 1.4 million residents, approximately 200,000 are aged between 15 and 25 [24].

Orygen HOPE aftercare has been operational since January 2022. To date, there has been no evaluation of this, or other youth-focused aftercare services, in Australia or internationally. The proposed evaluation will be the first to systematically evaluate an aftercare service for young people at high risk of suicide.

## Methods

### Study aims

The first aim of this evaluation is to assess the effectiveness of the youth-focused HOPE aftercare delivered by Orygen to reduce suicide-related behaviors and improve mental health outcomes among young people who have presented to ED following a significant self-harm event or a suicide attempt. Specifically, the primary objective is to evaluate the effectiveness of HOPE aftercare in reducing the frequency of suicidal ideation (primary outcome). The secondary objectives are to evaluate the impact of HOPE aftercare on hospital re-presentation rates, mental health outcomes, quality of life, and determine the cost-effectiveness and scalability of the intervention.

The second aim of this evaluation is to assess the implementation of the service. Specifically, to determine the feasibility of delivering the service, assess acceptability and satisfaction with HOPE aftercare, and identify contextual barriers and enablers.

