	What are the characteristics of the participating service system and health providers?	*Engagement (Staff)*	Characteristics of providers (e.g., age, gender, years of service, professional background, roles)	Demographic variables					X					
		*Service setting**characteristics*	Characteristics of the service setting (e.g., organizational climate and culture, service resources, leadership capacity, staff integration)	CFIR–IS ILS PSI					X					
		*Provider characteristics*	Characteristics of providers’ training, knowledge, self-efficacy and attitudes/perceptions about suicide	Purpose-developed items based on existing measures. ASP scale					X					
	What barriers/ facilitators exist, and how do they affect the program access, engagement and efficacy?	*Barriers/Facilitators*	Identification of barriers and facilitators	Open-ended questions		X		X		X				
Implementation	What are the contextual factors (i.e., organizational, system and individual) impacting implementation?	*Moderators*	Descriptors of changes or modifications to the intervention							X	X			
	How satisfied are young people/family members with the service?	*Satisfaction*	User satisfaction rates	Routinely collected data Purpose-developed questions		X		X	X	X		X		
	What level of delivery is the program achieving? What are the components getting delivered, are there any adaptations?	*Treatment adherence*	Descriptors of treatment components and methods of delivery	Purpose-developed questions							X			
	Is the service acceptable, appropriate and feasible from the perspectives of young people, support persons and providers?	*Acceptability*	Proportions of users and providers ratings	AAF Open-ended questions	X	X	X	X	X	X				
Effectiveness	For young people, does engaging with the service lead to: - Reduced self-reported self-harm, suicide ideation and attempts - Reduced re-presentations to ED - Improved mental health related to depressive symptoms and psychological distress? - Increased treatment engagement, social/vocational functioning and quality of life?	*Effectiveness*	Significant reduction from baseline to posttreatment on frequency and severity of suicidal ideations (primary outcome), and frequency and severity of self-harm and suicide attempts	SIDAS YRBS Self-harm (purpose-developed questions)	X		X							
			Significant reduction in hospital (re-)presentation trends to ED since the implementation of HOPE aftercare	Hospital (re)presentation rates (Surveillance data)										X

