		*Improved mental health*	Significant improvement on mental health indicators	PHQ–9 GAD–7 K10 PSS	X		X							
		*Better functioning*	Treatment completion and dropout rates Significant improvement in functioning and quality of life	CHU–9D	X	X					X		X	
	Is the service safe?	*Safety*	Significant deterioration of symptoms Occurrence of serious adverse events	SIDAS, suicide attempt or hospital admission	X								X	
	Is the service acceptable, appropriate and feasible from the perspectives of young people, support persons and providers?	*Acceptability*	Proportion of service users and providers	AAF	X		X				X			
	Is the service cost-effective?	*Cost-effectiveness*	Program costs and costs of additional healthcare services (i.e., hospital presentations and psychological treatment) relative to quality of adjusted life years.	Hospital re-presentation RUQ CHU–9D	X								X	X
Maintenance	What are the long-term effects of the service on individual outcomes?	*Effectiveness (at follow-up)*	Significant further reduction or maintenance of symptoms at follow-up on measures of intensity and severity of suicidal ideations (primary outcome) and suicide attempt, self-harm, and mental health indicators and quality of life	SIDAS YRBS Self-harm (purpose developed questions) PHQ–9 GAD–7 K10 CHU–9D	X								X	X
	What are the likely impacts of the service when delivered at scale and within the current service eco-system?	*Scalability*	Computer-based system dynamics model											X

*EOT form *routinely collected end-of-treatment form, *ROM *Routine Outcome Measure, *Hospital* patient’s electronic medical records, *SHMS *Self-Harm Monitoring System for Victoria, *CFIR–IS *Consolidated Framework for Implementation Research Inner Setting measures [28], *ILS *Implementation Leadership Scale [29], *PSI *Program Sustainability Index [30], *ASP *Attitudes to Suicide Prevention Scale [31], *AAF *Acceptability, Appropriateness and Feasibility measures [32], *SIDAS *Suicidal Ideation Attributes Scale [33], *YRBS *United States Centers for Disease Control and Prevention’s National Youth Risk Behavior Survey [34], *PHQ–9 *Patient Health Questionnaire–9 [35], *GAD–7 *Generalized Anxiety Disorder Scale [36], *K10 *Kessler Psychological Distress Scale [37], *CHU–9D *Child Health Utility–9D [38, 39], *RUQ * Resource Use Questionnaire [40]

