### Sample size and power

Based on a similar aftercare service developed for adults [22], we expect to detect a medium effect size of suicide ideation frequency reduction at the follow-up time point. To detect this effect, and assuming a correlation between baseline and follow-up measures of 0.5 and a drop-out rate of 30%, a sample of 184 young people will be needed.

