#### Primary outcome

*Suicidal ideation* will be measured using the Suicidal Ideation Attributes Scale (SIDAS; [29]). The SIDAS consists of five items (rated 0–10) each targeting an attribute of suicidal thoughts over the past month: frequency, controllability, closeness to attempt, level of distress associated with the thoughts, and impact on daily functioning. The SIDAS has demonstrated strong internal consistency and good convergent validity in a large online sample of Australian adults, including young people aged 18 and above [29].

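### The primary outcome is stated inconsistently in both attribute and time point, which leaves up to four candidate primary tests, and success by maintenance at follow-up is undefined

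*Protocol article*

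**What the plan says.** The protocol article describes the primary outcome, or the quantity that it is powered on, in six places.

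- **Study aims:** "the primary objective is to evaluate the effectiveness of HOPE aftercare in reducing the frequency of suicidal ideation (primary outcome"). No time point is given.
- **Table 1, Effectiveness row:** "Significant reduction from baseline to posttreatment on frequency and severity of suicidal ideations (primary outcome").
- **Table 1, Maintenance row:** "Significant further reduction or maintenance of symptoms at follow-up on measures of intensity and severity of suicidal ideations (primary outcome").
- **Sample size and power:** the effect to be detected is a "suicide ideation frequency reduction at the follow-up time point".
- **Primary outcome (Measures):** the SIDAS has five items rated 0–10, "each targeting an attribute of suicidal thoughts over the past month: frequency, controllability, closeness to attempt", plus distress and impact on daily functioning. The section does not say whether one item or a total is analysed, and it gives no scoring direction for the items.
- **Quantitative analyses:** a linear mixed model examines change in suicidal ideation across baseline (Time 1), discharge (Time 2) and three months after discharge (Time 3). No contrast is singled out as primary.

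**The concern.** A plan may leave details to a later analysis plan. Here, however, the article does state the primary outcome, more than once, and the statements disagree. Frequency is one SIDAS attribute, and none of the five is called severity or intensity, so the three descriptions cannot all refer to the same score. The time point is post-treatment in one place and follow-up in another. A later analysis plan could agree with one of these statements only by contradicting another.

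At stake is which result counts. The study follows one treated group over time, and its main effectiveness claim rests on this outcome. If the score and contrast are not fixed, they can be chosen after the results are seen. The power statement also concerns frequency at follow-up, so it does not cover the post-treatment criterion that Table 1 labels primary.

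The Maintenance row raises a separate question. It accepts maintenance as an alternative to further reduction, but nowhere says what would show it.

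**Working it through.** **1. The statements side by side**

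| Place in the article | Attribute | Time point |
|---|---|---|
| Study aims | frequency | none |
| Table 1, Effectiveness | frequency and severity | Time 1 to Time 2 |
| Table 1, Maintenance | intensity and severity | Time 3 |
| Sample size and power | frequency | Time 3 |
| Primary outcome | SIDAS, score not named | none |
| Quantitative analyses | suicidal ideation | all three, no primary contrast |

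Reading severity or intensity as a SIDAS total gives 2 scores (frequency item, total) × 2 contrasts (Time 1 to 2, Time 1 to 3) = 4 candidate tests.

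**2. False-positive chance if any of the four may be claimed**

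Assumptions: each test is two-sided at 5%, no true change, equal correlation ρ between test statistics. The article gives neither α nor ρ.

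- Independent tests: 1 − 0.95⁴ = 1 − 0.8145 = 18.5%.
- Correlated tests (simulation, four equicorrelated normal statistics, at least one beyond ±1.96): 15.6% at ρ = 0.5, 13.1% at ρ = 0.7, 11.4% at ρ = 0.8.
- Counting only results in the favourable direction (nominal 2.5%): 7.8%, 6.5% and 5.7%.

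The frequency item is part of any total, and all four contrasts share the baseline, so independence cannot hold and 18.5% is only an upper bound.

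**3. Completers implied by the plan**

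Inputs from Sample size and power: "a sample of 184 young people will be needed", "assuming a correlation between baseline and follow-up measures of 0.5 and a drop-out rate of 30" per cent. Completers: 184 × 0.70 = 128.8, so about 128.

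The figure of 184 itself does not follow from a one-group paired comparison. Taking medium as d = 0.5 and assuming two-sided 5% and 80% power, the standardised change is d/√(2(1 − r)) = 0.5/√(2 × 0.5) = 0.5. That needs 34 completers, and 34/0.70 = 48.6, so 49 recruited. It does arise from two independent groups of 64: 64/0.70 = 91.4, rounded up to 92, and 2 × 92 = 184. That is a separate matter. Below, only 184 and 30% are used, to obtain the completers.

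**4. Maintenance, if read as no significant worsening from Time 2 to Time 3**

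For a true worsening of δ SD, the standardised change is δ/√(2(1 − r)), where r is the Time 2–Time 3 correlation. The rule passes when a paired t-test (n = 128, two-sided 5%) does not show significant worsening. For δ = 0.2:

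| Assumed r (Time 2–Time 3) | Standardised change | × √128 | Rule passes |
|---|---|---|---|
| 0.3 | 0.2/√1.4 = 0.169 | 1.91 | 52.5% |
| 0.5 | 0.2/√1.0 = 0.200 | 2.26 | 39% |
| 0.7 | 0.2/√0.6 = 0.258 | 2.92 | 17% |

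The article's 0.5 is for baseline and follow-up. It gives no value for Time 2 and Time 3, hence the range. At r = 0.5 the rule passes 97.5% of the time with no change, 80% at 0.1 SD, 39% at 0.2 SD, 20% at 0.25 SD and 8% at 0.3 SD.

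**The case against.** The strongest reply is that the conflict is narrow. The instrument is the SIDAS throughout, and one mixed model is planned over three times. In the Maintenance row, the primary-outcome label may only tag the construct rather than declare a second primary test. This stands in part: the ambiguity concerns the score and the contrast, not the instrument or the model. It does not remove the clash between the Effectiveness row (post-treatment) and the sample size (follow-up), or between frequency alone and frequency with severity.

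A second reply is that the article never says any one significant test will be claimed, and that with a true standardised change of 0.5 and about 128 completers a paired test has over 99.9% power, so the choice of test would rarely matter. Both are fair. The error rate is conditional on selective claiming, and the ambiguity bites when the effect is small, absent, or differs between scores or times.

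A reader might also infer that the follow-up rule can hardly fail. The documents do not support that. The article never equates maintenance with a non-significant change: it could mean still significantly below baseline, a rule that can fail. Even on the lenient reading, a 0.2 SD relapse is detected about 61% of the time at r = 0.5, and a 0.25 SD relapse about 80%. Table 1 also has a Safety row in which significant deterioration on the SIDAS is an outcome of its own. Nor is the planned model incapable of showing maintenance: it yields an interval for the change from Time 2 to Time 3, and what is missing is a margin.

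**Conclusion.** The concern holds as a contradiction within the article. The attribute and the time point of the primary outcome both differ between sections, and neither the measures section nor the analysis section resolves them. Up to four tests could be presented as primary. If any significant one were claimed, the false-positive chance would be about 11–16%, assuming two-sided 5% tests and correlations of 0.8–0.5. A reader might take 18.5% as the expected rate, but it requires an independence that overlapping scores rule out. The sample-size statement does not cover the post-treatment criterion.

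Separately, maintenance is undefined and has no margin. On the lenient reading, a 0.2 SD relapse would pass about 39% of the time at r = 0.5, with a range from 52.5% at 0.3 to 17% at 0.7. That range depends on a correlation the article does not give and on a reading it does not state. It shows why a definition is needed, not what the investigators intend.

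**What to change.** Before outcome data are analysed, the investigators should:

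1. Name one SIDAS score, either the frequency item or the total. For a total, state the scoring direction of each item, since the article gives none and controllability may run opposite to the others.
2. Name one primary contrast from the mixed model, Time 1 to Time 2 or Time 1 to Time 3, and make the other score and time point secondary.
3. Align Study aims, both rows of Table 1, Sample size and power, Primary outcome, and Quantitative analyses with that choice, and base the sample-size text on the same score and contrast.
4. Update the registry entry if it differs.
5. Define maintenance as the upper 95% confidence limit of the Time 2 to Time 3 change (worsening positive), from the same model, lying below a margin that is pre-specified and justified.

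Which score, contrast and margin to use is for the investigators to decide. The aims and the sample size point to frequency, and the sample size to follow-up, while Table 1 also points elsewhere. What matters is that exactly one is fixed. The cost is wording changes, a restated sample-size basis and a possible registry update, with no new data.
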